## 4. Methods

We will use routinely collected electronic health record (EHR) data from primary care practices using TPP SystmOne software, covering approximately 40% of the population in England, linked at the individual level to NHS Secondary Uses Service (SUS) data on hospitalisations, and Second Generation Surveillance System (SGGS) data on SARS-CoV-2 test results. We will conduct cohort studies investigating kidney outcomes in people after recorded SARS-CoV-2 infection compared to both contemporary (2020-2021 general population) and historical (2018-2019 general population) groups.

### 4.1 Data source

Primary care records managed by TPP, a GP software provider, were linked to other data sources through OpenSAFELY, a data analytics platform created by our team on behalf of

NHS England to address urgent COVID-19 research questions (<https://opensafely.org>) (Williamson 2020). OpenSAFELY provides a secure software interface allowing the analysis of pseudonymized primary care patient records from England in near real-time within the EHR vendor's highly secure data centre, avoiding the need for disclosive pseudonymized patient data to be transferred off-site. This, in addition to other technical and organisational controls, minimizes any risk of re-identification. Similarly, pseudonymized datasets from other data providers are securely provided to the EHR vendor and linked to the primary care data. The dataset analysed within OpenSAFELY is based on 24 million people currently registered with GP surgeries using TPP SystmOne software. It includes pseudonymized data such as coded diagnoses, medications, and physiological parameters. No free text data are included. Further details on our information governance can be found here: [information governance and ethics](#).

## 4.2 Information governance

NHS England is the data controller; TPP is the data processor; and the key researchers on OpenSAFELY are acting on behalf of NHS England. This implementation of OpenSAFELY is hosted within the TPP environment, which is accredited to the ISO 27001 information security standard and is NHS IG Toolkit compliant (NHS Digital Data Security Standards, NHS Digital Data Security & Protection Toolkit); patient data have been pseudonymized for analysis and linkage using industry standard cryptographic hashing techniques; all pseudonymized datasets transmitted for linkage onto OpenSAFELY are encrypted; access to the platform is through a virtual private network (VPN) connection; the researchers hold contracts with NHS England and only access the platform to initiate database queries and statistical models; all database activity is logged; and only aggregate statistical outputs leave the platform environment following best practice for anonymization of results such as statistical disclosure control for low cell counts (NHS Digital Anonymisation standard for publishing health and social care data). The OpenSAFELY research platform adheres to the data protection principles of the UK Data Protection Act 2018 and the EU General Data Protection Regulation (GDPR) 2016. In March 2020, the Secretary of State for Health and

Social Care used powers under the UK Health Service (Control of Patient Information) Regulations 2002 (COPI) to require organisations to process confidential patient information for the purposes of protecting public health, providing healthcare services to the public and monitoring and managing the COVID-19 outbreak and incidents of exposure (Department of Health and Social Care Coronavirus (COVID-19): notification to organisation to share information). Together, these provide the legal bases to link patient datasets on the OpenSAFELY platform. GP practices, from which the primary care data are obtained, are required to share relevant health information to support the public health response to the pandemic and have been informed of the OpenSAFELY analytics platform.

### 4.3 Study designs

We will compare people after SARS-CoV-2 infection to both historical and contemporary cohorts in order to address epidemiological challenges and triangulate meaningful conclusions.

Testing for SARS-CoV-2 during the early stages of the pandemic was restricted due to a lack of infrastructure; therefore many people who were infected (both symptomatic and asymptomatic) will not have been coded as such and so will be misclassified in a contemporary comparison. Using historical comparator groups will allow us to definitively ensure that the comparator group was not infected with SARS-CoV-2 during follow-up. Some comparisons will also be matched on date (i.e., to start follow-up on the same date two years before), which will allow us to account for consistent seasonal variations.

Contemporary comparator populations will account for potential biases we anticipate for any historical comparison. Using a contemporary comparator will also allow us to finely adjust for changes over time during the pandemic (with time since the start of the pandemic as the underlying timescale), such as the emergence of SARS-CoV-2 variants, changes in testing policy, changes in treatment of COVID-19, and differences in ascertainment of outcomes due to reduced access to healthcare (including blood bottle shortages in 2021).

## 4.4 Study populations

Our overall study population will be all adults registered with primary care practices using TPP SystemOne software (Figure 1) since 1 February 2016. We will exclude all individuals with missing age, sex, or Index of Multiple Deprivation (IMD) as these are likely to indicate poor data quality. All individuals included will need to have at least three months of follow-up available before cohort entry to ensure reliable capture of baseline health status; we have been reassured by TPP that three months is sufficient for records to be updated and this will optimise power.

### 4.4.1 Exposure group

Our exposure group will comprise people with recorded SARS-CoV-2 infection identified using data from SGSS, primary care records or SUS who remain alive 28 days after the first recording of infection (i.e. 28 days after date of testing positive in SGSS, coding in primary care records, or admission on SUS) (index date) (Figure 1).

Anyone coded in primary care or SUS to be receiving chronic dialysis or kidney transplant or with  $\text{eGFR} < 15 \text{ ml/min/1.73m}^2$  (i.e. anyone with ESRD or CKD Stage 5) at the time of first recording of SARS-CoV-2 infection will be excluded.

A secondary analysis will investigate individuals who remain alive 28 days after the date of first hospital admission coded for COVID-19 in SUS. Anyone coded in primary care or SUS to be receiving chronic dialysis or kidney transplant or with  $\text{eGFR} < 15 \text{ ml/min/1.73m}^2$  (i.e. anyone with ESRD or CKD Stage 5) at the time of hospital admission will be excluded.

### 4.4.2 Historical comparator groups

For our main analysis, historical comparator groups will comprise individuals from the general population under follow-up in OpenSAFELY, each matched five to one to each

individual from the recorded SARS-CoV-2 group on age (within 2 years), sex, NHS Sustainability and Transformation Partnership (STP, geographical areas configured for regional reorganisation available in our data), IMD decile (a measure of socioeconomic deprivation based on postcode), and date (i.e. 2 years before the first recording of SARS-CoV-2 infection in the exposed case) (Figure 1). Anyone coded in primary care or SUS to be receiving chronic dialysis or kidney transplant or with eGFR  $<15$  ml/min/1.73m^2 before this date will be excluded (i.e. anyone with ESRD or CKD Stage 5). We will match without replacement (i.e. individuals in the historical comparator group will not be matched to more than one individual with SARS-CoV-2 infection) in order to optimise statistical precision.

In a secondary analysis, we will compare individuals who remain alive 28 days after admission to hospital with COVID-19 with those who remained alive 28 days after admission to hospital for pneumonia (including influenza) from 1 February 2018 up to two years before the end of follow-up for the exposed group (unmatched) (Figure 1). A previous study done using OpenSAFELY found similarities in outcomes between people discharged after hospitalisation with COVID-19 and a historical comparator group discharged after pneumonia. Individuals who survived COVID-19 and hospitalisation from pneumonia in 2018-2019 will be followed-up in both the exposed and unexposed groups.

#### **4.4.3 Contemporary comparator group**

For our main analysis, contemporary comparator groups will comprise individuals from the general population under follow-up in OpenSAFELY, individually matched five to one to each individual from the recorded SARS-CoV-2 group on age (within 2 years), sex, NHS STP, IMD decile, and date of first recording of SARS-CoV-2 infection (Figure 1). Anyone coded in primary care or SUS to be receiving chronic dialysis or kidney transplant or with eGFR  $<15$  ml/min/1.73m^2 before the first recording of SARS-CoV-2 infection will be excluded (i.e. anyone with ESRD or CKD Stage 5). We will again match without replacement. Individuals from this group will be censored if they themselves are recorded

with SARS-CoV-2 infection and further follow-up will commence in the exposed group from 28 days after recording if they remain alive (Figure 1).

#### **4.4.4 Follow-up start**

By using index dates 28 days after first recording of SARS-CoV-2 infection (i.e., date of testing in SGSS, date of primary care coding, or date of admission on SUS), we will be able to look back and further stratify the exposure by measures of SARS-CoV-2 severity (i.e. community, hospitalisation, critical care admission etc.).

For analyses comparing people after SARS-CoV-2 infection to a historical comparator group from 2018-2019, the matched historical comparators will be followed-up from exactly two years before the index date.

For analyses comparing people hospitalised for COVID-19 with an unmatched historical group of individuals hospitalised for pneumonia from 2018-2019, we will follow all eligible individuals from 28 days after their admission date for pneumonia.

For analyses comparing people after SARS-CoV-2 infection to a matched contemporary comparator group, we will follow all eligible individuals from the index date.

#### **4.4.5 Follow-up end**

In all analyses we will follow individuals until the earliest of: record of specific kidney outcome under investigation, ESRD, death, no longer registered with GP practice, or study end. Individuals from the matched contemporary comparator group will also be censored at the date of first recorded SARS-CoV-2 infection and will transfer to the exposed group if they survive 28 days after this date.

For analyses using matched historical 2018-2019 comparators, the study end for people with COVID-19 will be the last available date for data at the time of extraction, and for

their matched comparators it will be January 31 2020 at the latest. Our choice of end of follow-up for people with COVID-19 is to be consistent with the available follow-up time for people in the historical comparator group, as we will no longer be able to follow people in the historical comparator group after February 2020 (as we will no longer be sure that those in our comparator group did not have COVID-19 after the start of the initial UK COVID-19 outbreak in February 2020). By allowing the same duration of potentially available follow up for people with and without COVID we will be able to ensure our results are not biased by allowing additional follow up for people with COVID-19 (and consequently allowing more time for them to develop the outcomes under investigation) compared to those without. By allowing the same duration of potentially available follow up for people with and without SARS-CoV-2 infection, we will be able to ensure our results are not biased by allowing additional follow up for people pre-pandemic.

For analyses with the contemporary comparator group, the study end will be the latest available date of fully linked data available on the day the initial cohort is extracted.

[figure not shown]

[figure not shown]

*Figure 1* Graphical illustrations of potential study scenarios. **A-C: Examples of individuals with recorded SARS-CoV-2 infection.** A was followed-up from 28 days after SARS-CoV-2 infection until the study conclusion; B died within 28 days of SARS-CoV-2 infection so was not followed-up; C commenced follow-up from 28 days after SARS-CoV-2 infection until they were censored (i.e. for outcome event, death, or ESRD). **D-E: Examples of matched contemporary comparators.** D was matched to an individual with SARS-CoV-2 infection and followed-up from 28 days after matching until the study conclusion; E was matched to an individual with SARS-CoV-2 infection and followed-up from 28 days after matching until they were first recorded with SARS-CoV-2 infection themselves when they were censored from further follow-up as an unexposed comparator and then followed-up as an exposed case from 28 days after infection until the study conclusion. **F-G: Examples of matched historical comparators from 2018-2019.** F was matched to an individual with SARS-CoV-2 infection and followed-up from 28 days after matching until the study conclusion; G died within 28 days of matching so was not followed-up; H commenced follow-up from 28 days after matching until they were censored (i.e. for outcome event, death, or ESRD). **I-J: Examples of unmatched historical comparators hospitalised for pneumonia from 2018-2019.** I was followed-up from 28 days after admission for pneumonia until the study conclusion. J died within 28 days of admission for pneumonia so was not followed-up.

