### 3. Objectives

Overall, our aim is to investigate long-term kidney outcomes after recorded SARS-CoV-2 infection in the general population.

Our specific objectives are:

1. To describe the relative and absolute rates of ESRD (primary outcome) after recorded SARS-CoV-2 infection compared to both contemporary and historical groups, stratified by:
  - a. Hospitalisation for COVID-19
  - b. Critical care admission for COVID-19
  - c. Mechanical ventilation for COVID-19
  - d. Acute KRT associated with COVID-19
  - e. AKI associated with COVID-19
2. To describe the relative and absolute rates of a 50% reduction in eGFR, incident AKI, and death (secondary outcomes), after recorded SARS-CoV-2 infection compared to both contemporary and historical groups, stratified by:
  - a. Hospitalisation for COVID-19
  - b. Critical care admission for COVID-19
  - c. Mechanical ventilation for COVID-19
  - d. Acute KRT associated with COVID-19
  - e. AKI associated with COVID-19
3. To describe the relative and absolute rates of these outcomes after hospitalisation for COVID-19 compared to a historical hospitalised group, stratified by:
  - a. Critical care admission for COVID-19
  - b. Mechanical ventilation for COVID-19

- c. Acute KRT associated with COVID-19
  - d. AKI associated with COVID-19
- 4. To describe the relative and absolute rates of outcomes after recorded SARS-CoV-2 infection compared to both contemporary and historical groups stratified by:
  - a. Baseline eGFR
  - b. Diabetes
  - c. Age
  - d. Sex
  - e. Ethnicity
  - f. Socioeconomic deprivation
- 5. To describe the relative and absolute rates of outcomes after recorded SARS-CoV-2 infection compared to both contemporary and historical groups additionally stratified by:
  - a. Calendar time
  - b. Vaccination status

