## 4.5.2 Outcomes

### 4.5.2.1 Primary outcome

We will identify incident ESRD through codes for dialysis or kidney transplant using either primary care codes, or ICD-10 or procedural codes from SUS, or eGFR  $<15\text{ml/min/1.73m}^2$  in primary care.

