## 3. Death

We will describe rates of death as this is an important competing risk for outcomes. Date of death will be obtained using primary care records, which compared to the Office for National Statistics (ONS) (the gold standard), has previously been demonstrated to have 78% exact agreement and 99% agreement within 30 days. In case such accurate date coding practices have been affected by the pandemic, we will be able to link to the ONS date of death for 2020 data (we do not have access to ONS date of death linkage before 2019).

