### **4.6.3 Secondary analyses**

1. We will use Cox regression models to estimate cause-specific hazard ratios and 95% confidence intervals for the secondary outcomes i) 50% reduction in eGFR, ii) AKI and iii) death for individuals after SARS-CoV-2 (stratified as above) compared to individuals in the i) historical and ii) contemporary comparator groups.
2. We will undertake further Cox regression models for both primary and secondary outcomes with SARS-CoV-2 infection stratified by calendar time (i.e. February –

June 2020, July – September 2020, October – November 2020, December 2020 – February 2021, and March – January 2022) and vaccination status.

3. We will fit interaction terms to obtain cause-specific hazard ratio estimates for both primary and secondary outcomes stratified by age group, ethnicity, socioeconomic deprivation, diabetes and baseline eGFR.
4. For people who survive 28 days after hospitalisation for COVID-19, we will undertake an unmatched cohort analysis comparing kidney outcomes with a historical population followed-up from 1 February 2018 restricted to those who survived 28 days after a hospital admission for pneumonia (with or without influenza). This analysis will be stratified by critical care admission, mechanical ventilation, acute KRT and AKI, with additional adjustment for calendar month. The reason for this analysis is to investigate whether COVID-19 is responsible for long-term kidney outcomes to a greater or lesser extent than hospitalisation for other respiratory tract infections.

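### Follow-up stops at ESRD in every analysis, so the secondary outcome of death is, as written, death before ESRD and not all-cause death

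*Protocol*

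**What the plan says.** Section 4.4.5 (Follow-up end) gives a single rule for every analysis: "In all analyses we will follow individuals until the earliest of: record of specific kidney outcome under investigation, ESRD, death", with deregistration and study end completing the list. Contemporary comparators also stop at their own recorded infection. ESRD is listed separately from the outcome under investigation. The Figure 1 legend repeats this, describing people followed "until they were censored (i.e. for outcome event, death, or ESRD".

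Death is an outcome in its own right. Objective 2 in section 3 reads "To describe the relative and absolute rates of a 50% reduction in eGFR, incident AKI, and death (secondary outcomes", and the strata listed under it include critical care, AKI and "Acute KRT associated with COVID-19". Section 4.6.3 plans Cox models for "i) 50% reduction in eGFR, ii) AKI and iii) death for individuals after SARS-CoV-2 (stratified as above". The outcome definition in section 4.5.2.2 gives a reason for including death: "We will describe rates of death as this is an important competing risk for outcomes".

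Section 4.5.2.1 defines the terminating event broadly: "We will identify incident ESRD through codes for dialysis or kidney transplant", or a primary care eGFR below 15. The dialysis codes are not limited to chronic dialysis, whereas the baseline exclusions in sections 4.4.1 to 4.4.3 are.

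No section calls the outcome death before ESRD or lets the death analysis run past ESRD. The deviations table does not alter the stopping rule.

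**The concern.** ESRD does not prevent a death from being observed. Dates of death come from primary care records, with some ONS linkage, and remain available after dialysis starts. Under the written rule a person who reaches ESRD leaves the death analysis on that date, and a later death is not counted.

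The loss is unlikely to be even across groups. Matched comparators come from the general population, where the protocol assumes an ESRD incidence of 0.02%. The exposed strata defined by AKI, critical care or acute KRT can be expected to reach ESRD more often, particularly as an acute dialysis code after the index date meets the definition. If mortality is also higher after ESRD, the death hazard ratio and the absolute death rate in those strata would be pulled down. At stake is whether objective 2 reports the quantity it names.

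**Working it through.** **The plan's own figures.** The protocol gives no figure for death. Its only design figure is the ESRD power in Table 1, which this point does not touch. A two-sided two-proportion calculation at 5:1 reproduces that table (200,000 exposed, hazard ratio 1.6: 87.5% against the stated 88%), and it is unchanged by the fix.

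**Whole cohort.** Use a constant-hazard model over T = 2 years with ESRD hazard e, death hazard d before ESRD and r × d after it.
- Deaths counted = d/(d+e) × (1 − exp(−(d+e)T)).
- Deaths lost = integral from 0 to T of e × exp(−(d+e)t) × (1 − exp(−r d (T−t))) dt.
- e = 0.0002 per year is the protocol's 0.02% (section 5); reading it as annual is an assumption. d = 0.01 per year and r are assumptions.
- Counted: 1.980% of people. Lost: 0.0004%, 0.0008% and 0.0015% of people at r = 1, 2 and 4.
- Share of all deaths lost: 0.02%, 0.04% and 0.08%.

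**Severe strata.** Suppose a proportion p has ESRD at index and so contributes nothing to the death analysis. Take a one-year horizon and a death hazard of 0.08 without ESRD and r × 0.08 with it (both assumed).
- Rate under the written rule = 0.08.
- Rate with nobody removed = [(1−p)(1−exp(−0.08)) + p(1−exp(−0.08r))] / [(1−p)(1−exp(−0.08))/0.08 + p(1−exp(−0.08r))/(0.08r)].
- At r = 3: 1−exp(−0.08) = 0.07688, giving 0.96105 person-years; 1−exp(−0.24) = 0.21337, giving 0.88905 person-years.

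The document offers two reference values for p. Section 2.1 reports that 3% of inpatients needed KRT. Section 1.1 says around 10% of those with AKI needed short-term dialysis. Both describe admitted patients, not people alive at 28 days, so they are indicative only.
- p = 0.03, r = 3: 0.08098 / 0.95889 = 0.08445; 0.08/0.08445 = 0.947, so understated by about 5%.
- p = 0.10, r = 3: 0.09053 / 0.95385 = 0.09491; 0.08/0.09491 = 0.843, so understated by about 16%.

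| r (assumed) | Rate understated, p = 3% | Rate understated, p = 10% | Deaths lost, p = 3% | Deaths lost, p = 10% |
|---|---|---|---|---|
| 1 | 0% | 0% | 3.0% | 10.0% |
| 2 | 2.8% | 8.8% | 5.6% | 17.6% |
| 3 | 5.3% | 15.7% | 7.9% | 23.6% |
| 4 | 7.4% | 21.3% | 9.9% | 28.4% |

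The r = 1 row separates the two consequences. Deaths go uncounted whatever r is. The rate is unaffected when r = 1, because the person-time after ESRD is dropped along with the deaths. Where comparators lose almost nobody to ESRD, the hazard ratio for the stratum falls by roughly the same proportion as the exposed rate.

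**The case against.** The strongest reply is that the rule is right for the stated purpose. Death is described because it competes with the kidney outcomes, and the event that competes with ESRD is death before ESRD. A death after ESRD competes with nothing. Section 4.6.3 asks for cause-specific hazard ratios, which fits ending follow-up at the other event. This stands as far as it goes: a reader might infer that the rule spoils the competing-risk description, and it does not. But objective 2 also lists death, without qualification, as a secondary outcome with relative and absolute rates, and for that the rule gives a different quantity.

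A second reply is that the sentence was drafted with kidney outcomes in mind and was never meant to govern death. That may be so, but it says that it applies to all analyses and the figure legend repeats it.

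A third concerns size. A reader might infer a large, certain downward bias in the acute KRT stratum: with 30% or 50% in ESRD at index and a threefold hazard, the formula above gives 36% or 49%. The documents do not support these figures. They give no such proportions and no mortality ratio, and the deviations table records that acute renal replacement therapy and mechanical ventilation were not used as exposure levels in the end. That table also says acute renal replacement therapy in the first 28 days was counted as kidney failure on day 1. If the stopping rule was kept, some effect would remain in the AKI and critical-care strata, of unknown size.

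**Conclusion.** The point holds as a mismatch between a stated rule and a stated outcome. Followed as written, section 4.4.5 makes the death analysis one of death before ESRD, while sections 3 and 4.6.3 call it death.

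Counts of death, and cumulative risk taken as counted deaths over people at entry, are understated wherever ESRD occurs. It would go too far to say that death rates and hazard ratios are necessarily biased downward: that requires higher mortality after ESRD than before. Section 2.2 links CKD with higher all-cause mortality, which supports the direction without giving a size.

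In the whole cohort the effect is negligible, under 0.1% of deaths. In the severe strata the understatement of the rate runs from none, with equal mortality, to about 5% (p = 3%) or 16% (p = 10%) at a threefold hazard. These figures rest on the assumed hazards, on ESRD being present at index, and on inpatient proportions applied to 28-day survivors. The primary ESRD analysis is unaffected. The 50% eGFR outcome already includes ESRD, so stopping there is sound for it.

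**What to change.** Add a sentence to section 4.4.5: for death as a secondary outcome, follow-up runs to the earliest of death, deregistration, study end or, for contemporary comparators, recorded SARS-CoV-2 infection, and does not stop at ESRD. Leave the rule unchanged for the kidney outcomes.

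Keep the ESRD-ended hazard as well, labelled as death before ESRD, and use it only to describe the competing event for the ESRD analysis. State in section 4.5.2.2 which of the two quantities each reported death rate refers to.

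The cost is a sentence or two of text and one extra censoring variable. No new data are needed, since deaths after ESRD are in the same records.

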## 1.3 Strengths and limitations

As kidney failure is a relatively rare occurrence in the general population, very large studies are needed to be able to investigate whether or not a group is at increased risk compared to other groups. Because of the size of the population in OpenSAFELY, we are uniquely placed to be able to look for this in the context of COVID-19. Furthermore, we can expect the data to be comprehensive as it comes from GPs and hospitals within a national healthcare system with universal coverage.

As with other studies of this nature, we anticipate challenges associated with real-world data collection. We will be as rigorous as possible to address these limitations by undertaking multiple analyses with slight differences. For example, we will compare people with COVID-19 (including people hospitalised and not hospitalised) to different groups of people without COVID-19:

1. A historical group comprising individuals followed-up from exactly 2 years before the person with COVID-19. The reason for using a historical comparator group is because not everyone with COVID-19 gets diagnosed, especially when access to testing has been limited.
2. A contemporary group comprising individuals followed-up from the same time as the person with COVID-19. The reason for using a contemporary comparator as well is to account for changes over time during the pandemic such as differences in access to healthcare (e.g. likely to have the same access to blood tests).

A further historical analysis will be restricted only to people hospitalised with COVID-19. In this analysis, we will compare this group to people hospitalised with other lung infections from February 2018 onwards up to the start of the pandemic. This will help us understand whether any differences in kidney outcomes are specifically due to COVID-19 or due to having any lung infection severe enough to require hospital admission.

This particular study will not investigate outcomes in kidney transplant recipients. One of the reasons for this is because blood test results in OpenSAFELY come from GP records

rather than hospitals where many transplant patients have their tests done. We do intend to work around this with a different study design.

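### In the matched historical analysis, an open end date for people with COVID-19 against a fixed one for comparators does not secure the equal potential follow-up that section 4.4.5 claims; the pneumonia window also needs one consistent end

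*Protocol*

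**What the plan says.** Section 4.4.5 sets two end dates for the matched historical analysis. For the exposed, "the study end for people with COVID-19 will be the last available date for data at the time of extraction". The other group has a calendar limit instead: "their matched comparators it will be January 31 2020 at the latest". The section justifies the exposed end date by pointing to the historical group: "Our choice of end of follow-up for people with COVID-19 is to be consistent with the available follow-up time for people". The result it claims, freedom from bias through extra time in the COVID-19 group, rests on this premise: "By allowing the same duration of potentially available follow up for people with and without COVID".

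Section 4.4.4 fixes the offset: "the matched historical comparators will be followed-up from exactly two years before the index date". Sections 4.4.4 and 4.5.1 put the index date 28 days after the first record of infection.

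For the unmatched pneumonia comparison, section 4.4.2 takes admissions "from 1 February 2018 up to two years before the end of follow-up for the exposed group (unmatched"). The lay summary (section 1.3) describes the same cohort as "people hospitalised with other lung infections from February 2018 onwards up to the start of the pandemic". Section 4.4.4 and the Figure 1 legend both place it in 2018-2019. Section 4.4.5 gives no calendar end for pneumonia comparators, and no separate end for the exposed in that analysis.

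**The concern.** One group's follow-up stops on a fixed date and the other's on whatever date the data happen to end. With a fixed two-year offset, that cannot guarantee equal potential follow-up. Equality would depend on when the data were extracted, yet section 4.4.5 presents it as a property of the design and names extra exposed follow-up as a bias to be avoided.

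All the objectives in section 3 ask for absolute as well as relative rates. A rate averaged over a longer time since index is not comparable with one averaged over a shorter time if the hazard changes after acute illness, and an average hazard ratio has the same weakness. Section 4.6.2 does not mention stratifying the Cox model by matched set. On a time-since-index scale, late exposed time would then be set against only those comparators with long follow-up, who are matched to people infected early.

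The pneumonia window is a related but separate matter. If its end moves past January 2020, admissions with unrecognised COVID-19 could enter the comparator group. That is the risk section 4.4.5 gives as its reason for stopping historical follow-up.

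**Working it through.** The plan states no length of follow-up to reproduce. The statement to test is its claim of equality.

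**Inputs**
- Lag from first record to index: 28 days (sections 4.4.4 and 4.5.1).
- Offset: 2 years (section 4.4.4).
- Comparator end: 31 January 2020 (section 4.4.5).
- Exposed end: E, the last available data date (section 4.4.5). No date is given, so E is an assumption and a range is shown.

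**Formulas**
- Index = first record + 28 days.
- Exposed maximum = E − index.
- Comparator maximum = 31 January 2020 − (index − 2 years) = 31 January 2022 − index.
- Excess exposed time = E − 31 January 2022, the same for everyone whose index date precedes 31 January 2022.
- Pneumonia accrual limit under section 4.4.2, if the same E applies = E − 2 years.

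**Index dates.** Infection on 15 March 2020 gives index 12 April 2020; 1 July 2021 gives 29 July 2021; 15 December 2021 gives 12 January 2022. Their comparator maxima are 659, 186 and 19 days, whatever E is.

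**Results (maximum days, exposed v comparator)**

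| Assumed E | Excess | Infected 15 Mar 2020 | Infected 1 Jul 2021 | Infected 15 Dec 2021 | Pneumonia limit |
|---|---|---|---|---|---|
| 31 Jan 2022 | 0 | 659 v 659 | 186 v 186 | 19 v 19 | 31 Jan 2020 |
| 31 Mar 2022 | 59 | 718 v 659 | 245 v 186 | 78 v 19 | 31 Mar 2020 |
| 31 Jul 2022 | 181 | 840 v 659 | 367 v 186 | 200 v 19 | 31 Jul 2020 |
| 31 Dec 2022 | 334 | 993 v 659 | 520 v 186 | 353 v 19 | 31 Dec 2020 |

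**Is E likely to be after 31 January 2022?** The last calendar stratum in section 4.6.3 runs from March 2021 (the year is implied by the preceding stratum) to January 2022. An infection on 31 January 2022 has its index date on 28 February 2022, so follow-up of that stratum needs later data. This is an indication, not proof.

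**Cases without comparator time.** 3 January 2022 + 28 days = 31 January 2022. Two years earlier is the comparator stop date itself. Infections recorded from 3 January 2022 therefore have comparators with no follow-up.

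**The last stratum as a whole.** Infection on 1 March 2021 gives index 29 March 2021 and a comparator maximum of 308 days. Comparator time falls from 308 days at the start of the stratum to 186 for 1 July, 19 for 15 December and 0 from 3 January.

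**The case against.** The strongest reply is that the text is coherent on one reading. If data ended on 31 January 2022, where the last calendar stratum ends, follow-up would be exactly equal and the pneumonia window would close on 31 January 2020. The few January 2022 cases would simply contribute no time. That stands as the zero-excess row of the table. It does not rescue the wording, because section 4.4.5 names no date and leaves the property to chance.

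Four stronger readings are tempting and should not be made.

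- A reader might infer that the plan means to enrol pneumonia admissions from 2020. Section 1.3, section 4.4.4 and the Figure 1 legend all bound the cohort before the pandemic. Both end dates in section 4.4.5 are written for the matched analysis only. What remains is a conflict of wording with section 4.4.2.
- A reader might infer that late calendar strata have almost no comparator time. That is true near the end of the last stratum, not across it.
- A reader might infer that the hazard ratio is biased. Unequal administrative censoring need not bias a cause-specific hazard ratio under proportional hazards and independent censoring, and rates have person-time denominators. Distortion needs hazards that change with time since index. The documents do not quantify this, and no effect on a rate or ratio has been estimated here.
- A reader might infer that the conducted analysis was unbalanced. The deviations table reports a three-year offset with ends of 31 January 2023 and 31 January 2020, which are symmetric, and makes the historical comparison a sensitivity analysis. The point rests on section 4.4.5 alone, not on any difference from that table.

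**Conclusion.** The point holds for the matched historical analysis as written. Section 4.4.5 claims equal potential follow-up, but with a two-year offset its rules deliver this only if exposed follow-up ends on 31 January 2022, and no section says that it does. The excess is E minus 31 January 2022: none at the earliest date considered, 59 days at 31 March 2022, 181 at 31 July 2022 and 334 at 31 December 2022. These sizes depend on an extraction date that the document does not give. The consequence for absolute rates and average hazard ratios depends on hazards that vary with time since index.

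The pneumonia limb is narrower. Section 4.4.2 gives an accrual limit beyond January 2020 only if exposed follow-up in that analysis runs beyond January 2022. In that case it contradicts the other descriptions of the cohort, and section 4.4.5 supplies no calendar end to settle the matter.

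The power table is untouched: it uses a fixed incidence of 0.02%, with no follow-up time.

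**What to change.** In section 4.4.5, state that exposed follow-up in the matched historical analysis ends at 31 January 2020 plus the matching offset (31 January 2022 for two years). Include only index dates before that cap, which for two years means infections recorded up to 2 January 2022. The label of the last calendar stratum should follow.

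In sections 4.4.2 and 4.4.5, reconcile the pneumonia passages so that accrual and comparator follow-up both end by 31 January 2020, and name the exposed end date for that analysis.

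The cost is wording and one censoring date. Exposed person-time after the cap, and cases indexed on or after it, leave the historical analyses only; the contemporary analysis keeps them. The cap does not lengthen comparator time for late-2021 infections (still 19 days for 15 December 2021), so historical estimates for those months will remain thin.
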